### Data Collection and Management

All data will be collected and stored using the QualtricsXM (Qualtrics) digital platform. This platform enables direct exporting of data to a variety of formats (eg, Excel and SPSS). To promote data quality, respondents will be required to respond to all items on each page of the survey before proceeding to the next part of the study, which would ensure there are no missing data from completed cases. While excellent participant retention is expected since the study (including intervention) is brief and occurs contemporaneously, some participants may decide to quit prior to completion. If a participant has provided any data beyond the study information sheet, the case will be analyzed according to the study arm to which it was assigned, with missing data managed as described in Statistical Analysis (eg, intention-to-treat). However, this will not apply to participants who are excluded due to failed quality checks (see Eligibility Criteria) because these are designed to filter for cases that were not eligible but were enrolled in the study inappropriately (eg, “bots” or individuals who mask their global location with a virtual private network).

### Statistical Analysis

#### Missing Data and Data Quality

Missing data will be addressed using either full information maximum likelihood or Markov Chain Monte Carlo multiple imputation strategies [63]. In case there is a violation of missing at random in preliminary analyses (which is unlikely), we will incorporate strategies representing the missingness. We will further explore data quality in terms of outliers, measurement error, non-normality, and variance heterogeneity. Robust methods of analysis (eg, Huber-White robust standard errors) will be used, as appropriate [64]. For all multi-item measures, we will evaluate reliability prior to computation of the variable.

#### Analyses

The following analyses will be performed for the 3 aim statements:

**Aim 1**: We will use an LMM to examine the effect of the intervention on trust in science, controlling for specified covariates (see Covariates).

**Aim 2**: We will first examine the profiles of believability in our control and intervention group using latent profile analyses [65,66]. After determining the number of classes and identifying scientific versus nonscientific profiles, we will conduct path analyses linking the brief digital intervention to believability profiles and the mediator (trust in science).

**Aim 3**: We will first examine the outcome variables for Aim 3—intention to engage in NPBs. Although we expect these intention-based items to function as a monotonic scale that can be collapsed into a single variable, we will need to conduct exploratory factor analysis to determine whether this is the case. The number of factors identified will affect how this outcome is treated in the subsequent part of Aim 3.

We will also examine the mediation effect of believability profiles on the association between behavioral intentions, trust in science, and the primary outcome for Aim 3 (ie, intention to engage in NPBs) in the post-test. Next, we will conduct path analyses linking the brief digital intervention to believability profiles and the mediators (trust in science and believability profiles), and behavioral intentions in the post-test.

For both Aims 2 and 3, we will use model fit statistics (eg, root mean square error of approximation, comparative fit index, and Tucker-Lewis Index) and examine specific indices of ill fit (eg, modification indices). To increase power and maintain Type I error, we will adapt the posterior probability method (eg, partial *P* value) for formal mediation analyses with intervening variables [67]. We aim to elucidate key mediational chains between our mediators (ie, trust in science and believability classes), predictors (ie, behavioral intervention statement), and outcome (ie, intention to engage in NPBs) through this design, instead of simply looking at the link between the intervention and intention to engage in NPBs.

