### Conceptual Framework for the Proposed Study

Our prior research on COVID-19 misinformation identified 4 different COVID-19 belief profiles [17]. The “scientific” profile was the most common (~70% of the respondents), comprising individuals who reported high believability for a statement about the zoonotic origin of COVID-19 and low believability for misinformed narratives. The other 3 “nonscientific” profiles were not named and were instead numbered alongside conceptual descriptions. Profile 2 (~8% of the respondents) comprised individuals who reported high believability for all narratives, including the zoonotic statement and misinformed statements. Profile 3 (~12% of the respondents) comprised individuals who reported moderate believability for all narratives, and the lowest believability for the zoonotic statement of any profile (although it was still reasonably high, with a mean score of 4.59 on a scale of 1-7). Finally, Profile 4 (~10% of the respondents) was similar to Profile 2, except for a comparatively lower endorsement of the narrative that 5G networks caused the spread of COVID-19. Trust in science (a scale variable, scored from 1 to 5, and computed from a 21-item questionnaire) [37] was substantively associated with different profile memberships, after controlling for political orientation, religious commitment, race and ethnicity, gender, age, and education level. Compared to the scientific profile, each 1-point decrease in trust in science was associated with 5 (for Profile 3) to 14.3 (for Profiles 2 and 4) times higher adjusted odds of belonging to nonscientific profiles [17]. Therefore, we speculate that intervening at the level of trust in science will potentially nudge some individuals into the scientific profile.

However, whether trust in science will further affect individuals’ intention to engage in preventive NPBs via mediated beliefs in misinformation remains to be clarified. To the extent that some common narratives suggest that COVID-19 does not pose a serious health threat [17], such narratives may reduce the magnitude of “perceived severity” based on the health belief model. It is also notable that cross-sectional studies have suggested an association between perceived severity, self-efficacy, and COVID-19 NPBs in Turkey and Kenya [31,32].

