### Primary Study Outcomes

#### Trust in Science

Participants’ “trust in science” will be measured both before and after they view the intervention or placebo using the 21-item scale developed by Nadelson et al [37]. Our previous research has found that this scale is highly reliable for diverse, online, and crowdsourced respondents [17,21].

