### Sample Size

We will recruit 1,000 individuals using Prolific, which is the maximum sample size permitted for a nationally representative sample via this platform. This sample size will give allow us to detect small (Cohen’s d=0.18) differences between both groups with 80% power. This effect size would be more than sufficient for both analysis types, that is, LMM (linear mixed models) and path analyses, thus accounting for power and other sample size considerations common to path analysis (eg, overspecification) [61].

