### Allocation of Interventions

The allocation sequence will be managed using the Randomizer tool in the Qualtrics platform [62] to ensure a 1:1 allocation of participants to intervention (1) and control (0) arms, each comprising 500 participants. Allocation will occur after consent has been processed. Furthermore, the procedure is automated, thereby ensuring allocation concealment.

Although this is, in practice, a double-blind study since participants will be unaware that they are randomized and all study mechanics will be processed using a computer, analysts will not be blinded to the meaning of the assignment variable. However, 2 independent consultant analysts have been retained to verify all results and subsequent interpretation.

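### Aim 1 leaves pre-infographic trust out of its adjustment set; adjusting for it would cut variance by about 5% to 25% (assumed correlations 0.9 to 0.5) with no new data

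*Protocol article*

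**What the plan says.** The Trust in Science section states that trust "will be measured both before and after they view the intervention or placebo using the 21-item scale". The Trial Design section puts the whole trial into one session, so the two scores are taken minutes apart.

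The Aim 1 analysis is one sentence: "We will use an LMM to examine the effect of the intervention on trust in science, controlling for specified covariates". It points to the Covariates section. That section lists political orientation, religious commitment, demographic variables, COVID-19 history, perceived severity, self-efficacy and normative beliefs. Pre-infographic trust is not on the list. The Aim 1 sentence names no time term, arm-by-time term, constraint on baseline means or coefficient to be tested.

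On size, the Sample Size section says "We will recruit 1,000 individuals using Prolific" and gives this as the platform's ceiling for a representative sample. The Allocation of Interventions section describes "arms, each comprising 500 participants". The stated target is 80% power for "small (Cohen’s d=0.18) differences between both groups", followed by: "This effect size would be more than sufficient for both analysis types, that is, LMM (linear mixed models) and path analyses".

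The Data Collection and Management section keeps, in the assigned arm, anyone who gave data beyond the information sheet. The Missing Data section plans full information maximum likelihood or multiple imputation.

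**The concern.** Individuals are randomised, no clustering is described, and trust is a single score at each time. A mixed model for trust then has something to model as repeated only if both scores are outcomes. If the arms have free means at both times, the treatment effect is the arm-by-time term, which with complete pairs equals the difference in mean change. A covariate that is fixed within a person and enters as a main effect adds the same amount to both scores, so it cancels from that difference. The planned covariate control would then add nothing to the precision of the Aim 1 test.

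The pre-infographic score is likely to be the strongest predictor of the post-infographic score, and it is missing from the adjustment set. Trust is the first-listed primary outcome and the sample cannot be enlarged on this platform, so precision that costs nothing is worth taking.

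**Working it through.** **Inputs from the article.** 500 per arm (Allocation of Interventions); d = 0.18 and 80% power (Sample Size); trust scored before and after (Trust in Science).

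**Assumptions, because the article gives no value.** Two-sided 5% test; equal SD of 1 at both times; pre-post correlation r from 0.3 to 0.9; complete pairs; no covariates in the formulas.

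**The plan's own figure.** For a plain two-sample comparison, SE = sqrt(2/500) = 0.0632. Then 0.18/0.0632 = 2.846, and 2.846 − 1.96 = 0.886, which gives power of 81.2%. The smallest detectable d at 80% power is 2.80 × 0.0632 = 0.177. The stated figure reproduces, as a two-group test that uses neither the pre score nor the covariates.

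**Change score (free arm-by-time contrast).** The SD of a change is sqrt(2(1 − r)).

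**Post score adjusted for pre score.** The residual SD is sqrt(1 − r²).

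**Variance ratio, adjusted to change.** (1 − r²) / [2(1 − r)] = (1 + r)/2, which is below 1 for any r below 1.

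| r | Change: power at d = 0.18 | Change: detectable d | Adjusted: power at d = 0.18 | Adjusted: detectable d | Variance ratio |
|---|---|---|---|---|---|
| 0.3 | 67% | 0.210 | 85% | 0.169 | 0.65 |
| 0.5 | 81% | 0.177 | 91% | 0.153 | 0.75 |
| 0.8 | 99.4% | 0.112 | 99.7% | 0.106 | 0.90 |
| 0.9 | >99.9% | 0.079 | >99.9% | 0.077 | 0.95 |

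At r = 0.5, 0.8 and 0.9 the saving equals 1000/0.75 − 1000 = 333, 1000/0.90 − 1000 = 111 and 1000/0.95 − 1000 = 53 extra participants.

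The change score reaches 80% power at d = 0.18 when sqrt(2(1 − r)) is at most 0.18/0.1772 = 1.016. That means r of at least 1 − 1.032/2 = 0.484, or about 0.5.

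**Arm term averaged over both times, for comparison only.** The expected value is (0 + 0.18)/2 = 0.09 and the SD is sqrt((1 + r)/2). Power is 42%, 38%, 32% and 31% at r = 0.3, 0.5, 0.8 and 0.9, before covariates.

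**Check by simulation.** 150 trials of 1000 people were simulated (r = 0.8, true effect 0.18, one covariate explaining 30% of variance) and fitted with random-intercept models.
- Arm-by-time contrast: mean estimate 0.173, SE 0.040. Adding the covariate as a main effect changed the estimate by at most 5e-15 and the SE by less than 1e-6.
- Mixed model with a common pre-infographic mean, with the covariate: 0.174, SE 0.037.
- ANCOVA with the covariate: 0.174, SE 0.037.
- Arm term in a model without interaction, with the covariate: 0.090, power 45%.

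**The case against.** **An article condenses the plan.** Model terms and the tested coefficient commonly sit in the SAP, so silence on them is not a fault. That stands for the unnamed contrast. It does not cover the adjustment set, which the article does fix by pointing to its covariate list; that list lacks the baseline score.

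**The change score is sound.** It is valid under randomisation and meets the stated d = 0.18 whenever r is about 0.5 or more. The same scale in one sitting makes a high r plausible, and at r of 0.8 to 0.9 the loss is only 5% to 10% in variance. Aim 1 also expects a moderate effect, for which power would be higher still. All of this stands and limits the weight of the point.

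**A reader might infer that the planned Aim 1 effect is halved.** The documents do not support that. Halving occurs only if an arm term averaged over both times is tested, and the text does not say it will be. With 0/1 coding and an interaction, the arm coefficient would be the baseline difference, expected to be zero, and the effect would be in the interaction.

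**A reader might also infer that the covariates can never help.** That goes too far. A mixed model with a common baseline mean is not excluded by the text, matches ANCOVA and does gain from covariates. Covariate-by-time terms can help where a covariate predicts change, and covariates can help in part with incomplete pairs.

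**Trust is also the mediator in Aims 2 and 3.** Those aims use path analyses, so the choice of contrast in the Aim 1 model does not carry over to them.

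**Conclusion.** The point holds as an improvement that needs no new data, not as an error. On the most natural reading, the Aim 1 model omits a baseline score that the trial already collects, and its arm-by-time contrast is a change score. Baseline adjustment lowers the variance by 25%, 10% and 5% at r = 0.5, 0.8 and 0.9. It keeps power above 80% at d = 0.18 over the whole range examined, whereas the change score falls short if r is under about 0.5 (67% at r = 0.3).

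These sizes rest on the assumed correlation, equal SDs, a two-sided 5% test and complete pairs. If r is high, as is plausible here, the gain is small. The far larger loss from an averaged arm term (power of roughly 31% to 42% before covariates) is a reason to name the contrast. It does not describe what the protocol plans.

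**What to change.** In the Aim 1 entry of the Analyses section, define the test as the arm difference in post-infographic trust, adjusted for pre-infographic trust and the listed covariates. Two forms keep partial cases as the Data Collection and Management section intends:

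- a mixed model with both scores as outcomes and one common pre-infographic mean for the two arms, testing the arm difference at the post measurement; or
- ANCOVA of the post score on arm, pre score and covariates, with the multiple imputation already planned and robust standard errors where needed.

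ANCOVA on complete cases alone would drop people without a post score, so it should not be used without the imputation. The cost is one or two sentences of analysis text, with no new data and no change to the sample size.

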Specifically, we will expand on current knowledge by assessing whether exposure to a brief informational statement (in the form of an infographic) about the scientific process can increase trust in science, reduce the likelihood of believing scientifically implausible narratives about COVID-19, and increase intentions to engage in recommended COVID-19 NPBs. Given the scale and scope of the pandemic, an intervention with a small effect size, if feasible to deploy within the cost-effective US social media infrastructure, would have the potential to save lives through increased adherence to NPBs. However, it is important not to rush the deployment of brief social media campaigns without careful research and planning to verify efficacy, given that such campaigns could have iatrogenic effects even when designed by scientists and media experts [34,35]. This echoes the recent findings by Lane and Fauci [36], who remind researchers even in the context of a pandemic, it is important to generate scientifically sound evidence.

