### Study Intervention

#### Infographic Design

The primary intervention in this study will be an infographic that is designed to build trust in the scientific process. Infographics are preferable to narratives or text because they focus on visuals as part of the storytelling process and facilitate cognitive information processing, knowledge absorption, and enhanced persuasion [48-50]. The infographic design used in this study will follow best practices in health communication. The message communicated will be simple and jargon free. The infographic will comprise visuals of individuals (scientists), charts, text, and numerical data [48]. Attention will be paid to the images used, color, frames, representation, and composition (eg, how the elements in the infographic are organized to show their relationship to each other) [49]. The design process will be completed in the following 2 stages (note that these are development stages, not trial stages).

#### Stage 1

Sample concepts and messaging will be created based on the core constructs underlying the trust in science inventory [37]. The messages will assume divergent approaches to clarify what science is, how the scientific process operates, and how science is a self-correcting process. This content may focus, for example, on how the self-correcting elements of science serve to enhance people’s quality of life (eg, addressing items 1 and 21 from the inventory [37]). In such a case, the accompanying visuals might demonstrate a flat earth progressing to a globe, and then to a picture of the earth captured from a space station. These messages will be informally discussed by the authors’ nonscientific social network in preparation for a formal pilot study.

#### Stage 2

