#### Believability Profiles

Next, participants’ “believability profiles” will be computed via a latent profile analysis of the believability measures described below, which will be administered after the infographic is viewed. The measures and approach used to conceptualize believability of misinformation were developed and first used in our recent study on COVID-19 narratives [17]. As in the original study, we will not prespecify the existence of certain profiles, although we do expect to identify similar profiles in this study (potentially with differences introduced by the additional metrics described subsequently).

Response options for all believability measures will use well-established semantic differential responses for believability of different statements (eg, as used by Herzberg et al [53]), ranging from 1 (“extremely unbelievable”) to 7 (“extremely believable”). The original measures [17] assessed the believability of 4 statements related to COVID-19 that were derived from common pieces of misinformation (as of April 2020), as identified by a team at Cornell University [54]. For instance, one of the statements was, “The recent rollout of 5G cellphone networks caused the spread of COVID-19.” Another statement asked subjects about their believability of a particular statement reflecting scientific consensus (ie, the zoonotic origin of the virus). Our ability to use latent profile analysis to generate plausible and conceptually meaningful subgroups with a good model fit points toward a certain degree of validity of these questions. This is noteworthy especially given the existence of a latent profile that generally believed the scientific consensus explanation and no other narrative (which would be less likely with invalid questions). Therefore, in this study, we will assess participants’ believability of the following 6 statements, which include slightly modified versions of the 4 above-referenced statements, as well as 2 new statements based on scientific findings clarifying emergent, persistent misinformation about the use of face masks to prevent COVID-19 spread [55-57]:

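### Aim 2 is judged by profile membership alone, so a fall in belief in the one consensus statement can go undetected

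*Protocol article*

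**What the plan says.** The Aim 2 hypothesis (Study Aims and Hypotheses) concerns belief in implausible narratives, takes profile membership as its evidence, and expects partial mediation by trust in science. Under Analyses the steps are: "After determining the number of classes and identifying scientific versus nonscientific profiles, we will conduct path analyses linking the brief digital intervention" to the profiles and the mediator. No contrast on a single statement is described.

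The profiles come from ratings on a 1 to 7 scale, given once, after the infographic. The section Believability Profiles announces six statements but lists seven; I work from the list. Six are misinformation. The seventh, zoonotic origin, is the true one, described for the prior study as follows: "Another statement asked subjects about their believability of a particular statement reflecting scientific consensus". The article does not fix the profiles in advance and gives no rule for how high zoonotic belief must be for a profile to be called scientific.

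The Conceptual Framework section describes the prior study's profiles. The scientific one (about 70%) combined high zoonotic belief with low belief in misinformation. Profile 2 (about 8%) showed "high believability for all narratives, including the zoonotic statement and misinformed statements". Profile 4 (about 10%) was similar except on 5G. Profile 3 (about 12%) had "the lowest believability for the zoonotic statement of any profile (although it was still reasonably high, with a mean score of 4.59" on the 1 to 7 scale).

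**The concern.** If zoonotic belief was fairly high in every prior profile, it can do little to separate them, and membership is decided mainly by the six misinformation ratings. Two things follow. A person who comes to doubt the zoonotic statement will usually stay in the same profile. A person who comes to doubt all seven statements moves, if anywhere, towards the scientific profile. Aim 2 alone then cannot tell better discernment from general scepticism.

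The protocol gives reasons to care. It warns that "such campaigns could have iatrogenic effects even when designed by scientists and media experts", and treats this as a reason to verify efficacy before deployment. One planned message is "how science is a self-correcting process", which might lower confidence in a current consensus claim. Under Next Steps, support for any one hypothesis is enough to make dissemination the next step, so a misleading Aim 2 result could lead to roll-out.

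**Working it through.** **1. The plan's own figure.** The article states "We will recruit 1,000 individuals using Prolific", 500 per arm, and "d=0.18) differences between both groups with 80% power". Alpha is not stated; I assume 0.05 two-sided.

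- Standard error of a standardised difference: sqrt(2/500) = 0.0632.
- Detectable d at 80% power: (1.960 + 0.842) × 0.0632 = 0.177.
- Power at d = 0.18: 81.2%. Required n: 485 per arm, 970 in total.

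The stated figure reproduces.

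**2. Which way a uniform fall pushes membership.** In a latent profile model with class-invariant, independent residual variances, the log odds of the scientific profile S against profile k are a constant plus the sum over items j of (mean in S − mean in k) × rating / variance. If all ratings fall by δ and the variances are equal, the log odds change by

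δ × [sum of the six misinformation gaps (k − S) − zoonotic gap (S − k)] / variance.

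The lowest prior zoonotic mean was 4.59 and the scale ends at 7, so the zoonotic gap cannot exceed 7 − 4.59 = 2.41. A uniform fall therefore pushes towards the scientific profile whenever the misinformation gaps average more than 2.41 / 6 = 0.40 points per item. Profiles described as low against moderate or high belief should clear that easily. With the means assumed in set 1 below, for example, the gaps to Profile 3 are 2.3 + 2.3 + 2.2 + 2.3 + 2.2 + 2.0 = 13.3 for misinformation and 5.5 − 4.59 = 0.91 for the zoonotic item. This gives direction only. It does not say how many people stand close enough to the boundary to cross it, and it ignores any new profile in the refitted model.

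**3. How much (simulation).** Inputs from the article: 500 per arm, shares of 70/8/12/10%. Set 1 also uses the 4.59 mean. All other item means and SDs are assumptions. Four profiles were fitted by EM with modal assignment, and arms were compared without covariates. Every set required a reasonably high zoonotic class mean for the scientific label (above 4 in set 1, at least 4.5 in sets 2 and 3).

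- Set 1: item-specific SDs, independent errors, 50 trials per scenario.
- Set 2: SD 1.2, independent errors, 60 to 80 trials.
- Set 3: as set 2, plus a general credulity factor with SD 0.7.

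| Shift in intervention arm | Set | Scientific share, control vs intervention | Significant benefit | Significant harm |
|---|---|---|---|---|
| None | 1 | 69.3% vs 69.4% | 4% | 0% |
| All items −0.5 | 1 | 69.3% vs 69.8% | 6% | 6% |
| All items −0.5 | 2 | 69.0% vs 70.6% | 10% | not tabulated |
| All items −0.5 | 3 | 69.6% vs 74.6% | 40% | not tabulated |
| All items −0.8 | 2 / 3 | not tabulated | 25% / 75% | not tabulated |
| All items −1.0 | 1 | 69.7% vs 72.9% | 28% | 2% |
| Zoonotic only −0.5 | 1 | 70.1% vs 69.6% | 2% | 8% |
| Zoonotic only −0.5 | 3 | 70.7% vs 70.8% | not tabulated | never |
| Zoonotic only −1.0 | 1 | 70.0% vs 67.3% | 2% | 30% |

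After rounding and clipping to 1 to 7, the 0.5-point uniform shift lowered the mean zoonotic rating by about 0.45. Further runs of that shift with other assumed means gave 68.9% vs 71.8% (independent errors) and 59.5% vs 69.2% (credulity factor). Across all runs of it, significant benefit ranged from 6% to 90%.

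A direct arm comparison of the zoonotic item was significant in every run of the four shifted scenarios in set 1, and in essentially every run in sets 2 and 3. With no shift it was significant in 10% of 50 runs, that is 5 runs against 2.5 expected.

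**4. Is the direct contrast powered?** The detectable difference is 0.177 × SD: 0.18, 0.27 or 0.35 points for an assumed SD of 1.0, 1.5 or 2.0. The post-exposure rating is enough, because the arms are randomised.

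**The case against.** A reader might infer that an infographic which made people doubt science altogether could pass unseen. The article does not support that. Trust in science is a primary outcome, measured before and after exposure on a 21-item scale, tested by arm in Aim 1 and used as the Aim 2 mediator. The pilot also looks at trust, believability and perceived meaning. What can go unseen is narrower: a fall in belief in a specific consensus claim without a fall in general trust.

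Nor is the zoonotic item ignored. High belief in it was part of the description of the prior scientific profile, and a distinct all-low profile, if one emerged, need not be called scientific. This stands, but it does not close the gap. No labelling rule is given, and a profile's mean can stay high while one arm's mean falls. It would also be too strong to say that the item never affects membership: a 1-point fall in it alone was flagged as harm in 30% of runs in set 1.

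The Aim 2 hypothesis names only implausible narratives, so the analysis does match its aim. The point is what may be concluded from it, given the protocol's own warning about iatrogenic effects.

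The false-benefit rates are fragile. They depend on item means the article does not give, on a credulity factor it does not mention, and on imposing four profiles. When BIC chose the number of profiles in credulity-factor runs, four was never selected (0 of 45), although significant benefit still occurred in 7 of 15 uniform-shift runs. Nothing in the article suggests that one brief exposure would lower every rating by 0.5 points or more. That a message on self-correction breeds blanket doubt is possible, not shown.

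Finally, an item-level contrast may sit in an analysis plan that is not shown. The article nevertheless fixes what counts as evidence for Aim 2, and that choice is what is at issue.

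**Conclusion.** The point holds in limited form. Scientific versus nonscientific membership is the only Aim 2 evidence the article describes, and the six misinformation ratings mainly drive it. A fall of about half a point in the consensus item can go undetected, and a uniform fall in all items can leave the scientific share unchanged or raise it. The direction follows from the prior profiles and the scale limit, given roughly equal residual variances and profiles like the prior ones. The size does not: the rise in the scientific share for a uniform 0.5-point fall ran from 0.5 percentage points (69.8 − 69.3) to 9.7 (69.2 − 59.5), depending on assumptions. No single false-success rate should be quoted as the trial's. The point is worth acting on, because the item is already collected and dissemination may follow from any one supported hypothesis.

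**What to change.** In Analyses, Aim 2:

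- Prespecify an arm contrast with confidence interval on the zoonotic statement (1 to 7). Report it beside the profile result and consider it when Aim 2 is interpreted.
- Add, as a supportive analysis, a discernment score: the zoonotic rating minus the mean of the six misinformation ratings.
- State that a profile is labelled scientific only if its zoonotic belief is high.

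The labelling rule alone would not suffice, since the simulations already applied one. A non-inferiority margin as a condition of Aim 2 success and additional survey statements are not needed. The cost is one extra model on an item already collected and a slightly more qualified Aim 2 claim, with no added participants or survey time.
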